### Expected Results

#### Primary Endpoint

The PaO_2_/FiO_2_ is classified into 3 categories of severity: severe (≤100 mm Hg), moderate (>100-≤200), and mild (>200-300). The PaO_2_/FiO_2_ is frequently calculated and considered a reflection of lung injury, and low PaO_2_/FiO_2_ is associated with more PPCs and mortality. Previous studies revealed that a PaO_2_/FiO_2_ decrease of 10% from baseline was clinically meaningful. The investigators note the lowest PaO_2_/FiO_2_ within 48 hours after ICU admission as the primary outcome and take a difference of 30 mmHg (considering the normal value >300 mmHg) between the 2 groups as clinically significant.

### Secondary Endpoints

The European taskforce published guidelines for perioperative clinical outcomes (EPCO) (Table 3)^12^; PCCs after surgery include ARDS, noncardiogenic pulmonary oedema, pulmonary infection, pneumonia, pleural effusion, atelectasis, and respiratory failure. The composite of these events is considered as the secondary endpoint of this study. Other secondary outcomes will include the duration of mechanical ventilation, ICU and hospital stay, and patient mortality within 7 postoperative days. Time-weighted average of PaO_2_/FiO_2_ ratio within the first 48 hours will also be followed as an additional outcome.

### Data Collection

Clinical and demographic variables, including age, BMI, gender, ejection fraction, comorbidities, and echocardiographic assessments, will be collected. Arterial blood gas will be collected in the preanaesthesia clinic, before incision and CPB, on CPB, and after CPB until skin closure. Arterial blood gas will also be performed at ICU admission (as 0 hour postoperatively) and at 4 hours, 8 hours, 12 hours, 18 hours, 24 hours, 36 hours, and 48 hours after ICU admission. Ventilatory parameters that will be recorded include FiO_2_, tidal volume, respiratory rate, PEEP, I : E ratio, pH, PaO_2_, PaCO_2_, HCO_3_, BE, and SpO_2_. Every patient will get a chest x-ray upon postoperative ICU admission as baseline. All pulmonary complications will be diagnosed based on the EPCO definitions. Intensivists who will assess, collect, and analyse data are blinded to the group assignment.

All collected information will be recorded in an electronic case report form (eCRF). After de-identification of all data, eCRFs will be securely stored at an online database. Trained research fellows will be responsible for building and maintaining the eCRFs. Each PI is responsible for monitoring the data entry for completeness, timeliness, and accuracy. For PPC diagnosis, training to all assessors will be provided, and interrater reliability checks between the assessors will be performed.

### Reporting of Compliance and Adverse Events

A trained research fellow/study coordinator will monitor protocol compliance, occurrence of protocol violation, and reporting of adverse events to the IRB.

### Follow-up

Subjects will be contacted via telephone by trained study team members on postoperative day 7 if the patient is already discharged from the hospital at that time.

## Discussion

There are 500 000 cardiac surgeries a year in the USA alone. Almost every patient has lung injury, and up to 25% of them develop PPCs after cardiac surgery.^13^ Most of prior studies focus on postoperative mechanical ventilation strategies and incidence of PPCs and mortality in the ICU.^14,15^ Postoperative pulmonary complications are mainly attributed to ventilation-induced lung injury (VILI) and ventilator-associated pneumonia (VAP). Both VILI and VAP are highly time dependent and are most common in patients who are ventilated for longer than 48 hours postoperatively. A protective mechanical ventilation strategy or an adaptive support ventilation triggered by spontaneous breathing is wildly accepted and applied to wean patients in the ICU.^15, 16^ Nowadays, patients are usually extubated within 6 hours postoperatively after an uneventful CABG. Therefore, the intraoperative mechanical ventilation has become an important proportion of overall mechanical ventilation.^17,18^ Therefore, the intraoperative ventilatory management might have significant impacts on outcomes after CABG even more than the ICU management.

Several studies suggest that a protective ventilation strategy is beneficial and can reduce PPCs, but some studies found no improvement or even increased mortality in cardiac patients with the protective ventilation strategies.^5,19^ The most significant ventilation parameter change between intra- and postoperative period is FiO_2_, and scarce data currently exist to evaluate the relationship between intraoperative FiO_2_ and PPCs in cardiac surgery.

Previous studies on FiO_2_ have diverse definitions of hyperoxia. Some studies’ criteria for hyperoxia are in the normoxia range for other studies.^20^ There are no well-established PaO_2_ targets on CPB, and clinical practice is highly variable. Based on the oxygen haemoglobin dissociation curve of normal subjects, SpO_2_ decrease from 100% to 90% will decrease PaO_2_ by 40 mmHg. We choose a minimum SpO_2_ of 95% as our safe threshold because it is close to PaO_2_ 80mmHg. The PaO_2_ from ABG is more accurate and reliable but cannot be monitored continuously; thus SpO_2_ is a more feasible and appropriate index for FiO_2_ adjustments.

The major limitation of this study lies in the difficulty of balancing many confounding factors during CABG with CPB that are harmful to the lungs, including the surgical procedure, CPB, hypothermia, blood contact with artificial surfaces, ischaemia–reperfusion injury, administration of blood products, and lung collapse.^21^ In our protocol, if the patient develops haemodynamic instability which requires a return to CPB or suffers circulatory arrest, they will be withdrawn from the study. We will also withdraw patients who require mechanical circulatory support systems like extracorporeal membrane oxygenation, ventricular assist device, or an Impella device for similar reasons. Transfusion is common in cardiac surgery, but CABG has a relatively low transfusion rate compared to other open-heart surgeries.^22^ Transfusion-associated lung injury (TRALI) has been well defined, and it is a prominent factor for increased morbidity and mortality.^23,24^ The reported incidence of TRALI varies widely, ranging from 0.0008% to 1.2% per unit of blood product administered and from 0.08% to 8% per transfused patient.^25^ Since transfusion of blood products, in particular blood plasma, may cause lung injury, these patients will also be withdrawn from our analysis. We predict a high rate of withdrawal, not only for safety reasons but also for bias control and balancing of confounding factors. Another study limitation is our inability to blind the anaesthesiologist. Only ICU physicians and research fellows/study coordinators who assess the outcomes will be blinded.

There exists increasing evidence that a restrictive oxygenation strategy may be beneficial in various groups of patients.^26^ It is important to understand the relationship between FiO_2_ and lung injury after cardiac surgery. This is one of the first randomised controlled trials to prospectively evaluate the influence of high inspired oxygen concentrations on pulmonary outcomes and oxygenation after cardiac surgery.

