Postoperative pain management will be provided as a bolus of 25 μg fentanyl, 0.2 mg hydromorphone intravenously, a continuous opioid infusion as needed, or 5-10 mg hydrocodone or oxycodone with acetaminophen orally with the aim of a visual analogue score less than 4. The goal is to achieve adequate pain control without respiratory compromise. Only normal saline, lactated Ringer’s solution, human albumin, or cell saver blood are allowed as maintenance infusion fluids during and after surgery. Fluid infusion rate from CPB weaning until the end of surgery should be less than 10 mL kg^–1^ h^–1^ to avoid pulmonary oedema; otherwise, the patient will be withdrawn from analysis. The trigger for transfusion of allogeneic red blood cells is 7 g dL^–1^ during CPB and 8 g dL^–1^ while not on CPB. The trigger for transfusion of plasma, cryoprecipitate, and platelets is determined by the laboratory values and clinical protocols. Transfusion of more than 2 units of red blood cells (RBCs), fresh-frozen plasma, platelets, or cryoprecipitate within 48 hours of ICU admission will result in withdrawal from the study.

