### Safety Assessment

The PI, investigators, study coordinators, attending anaesthesiologists, and intensivists will be in close communication throughout the entire procedure until patient discharge to ensure protocol adherence. Patients will be withdrawn intraoperatively if they require 1 lung ventilation, additional procedures other than CABG, circulatory arrest, repeated episodes of CPB support, or usage of circulatory assist devices. If a patient suffers an SpO_2_ < 90% for more than 5 minutes at any time during the surgery, the patient will be withdrawn, and this will be recorded as a serious adverse event. Postoperatively, if a patient experiences delayed extubation (i.e., weaning/extubation period lasting longer than 48 hours) or requires reintubation for non-respiratory reasons (i.e., surgical reasons), suffers major bleeding (i.e., requiring a delay in extubation due to haemodynamic management), and develops heart failure, they will be withdrawn. If there is a perioperative allogenic RBC transfusion of more than 2 units or if a patient receives any other blood products, the patient will also be withdrawn (Table 2). Other postoperative events such as AKI, stroke, myocardial infarction, reoperation, and sternal wound infection will be recorded as adverse events and be analysed to determine whether they are related to the intervention. A trained research team member (i.e., fellow, study coordinator) will monitor the protocol compliance and report any adverse events to the IRB.

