### Statistical Analysis

#### Sample Size Calculation

A decrease of 10% in PaO_2_/FiO_2_ from the baseline is considered as clinically significant. The ARDS definition is PaO_2_/FiO_2_ less than 300 mmHg; thus, a difference of 30 mmHg of mean value of the lowest PaO_2_/FiO_2_ postoperatively between the 2 groups will be considered as clinically significant. Assuming SD of 60 mmHg, *α* = 0.05, and 80% power with 2-sided *t*-test, at least 160 subjects will be needed in total to detect a difference (80 patients in each group). Considering potential withdrawal, protocol violation, and failure to follow-up, we will aim to recruit 200 patients (100 patients in each group) for this study.

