## Figures and Tables

**Figure 1. f1-tjar-51-2-112:**
[figure not shown]
Algorithm and timetable for enrolment, allocation to restrictive or liberal oxygenation groups, intraoperative management, and postoperative data collection.

**Table 1. t1-tjar-51-2-112:** The Schedule of Enrolment, Interventions, and Outcome Assessment in Different Periods of This Trial

	Enrolment	Allocation	Post-allocation			Close-out
Timepoint	Preoperative 1 Day Before Surgery	Before Oxygenation	Intraoperative	Postoperative 0 hours, 4 hours, 8 hours,12 hours, 24 hours, 48 hours	Discharge	Postoperative 7 Days
Enrolment						
Eligibility screen	**X**					
Informed consent	**X**					
Allocation		**X**				
Interventions						
Restrictive oxygenation group			**X**			
Liberal oxygenation group			**X**			
Assessments						
PaO_2_/FiO_2_ (ABG)		**X**	**X**	**X**		
Postoperative pulmonary complications				**X**	**X**	
Length of mechanical ventilation					**X**	
ICU stay					**X**	
Hospital stay					**X**	
Mortality						**X**

ABG, arterial blood gas; ICU, intensive care unit.

**Table 2. t2-tjar-51-2-112:** Inclusion, Exclusion, and Withdrawal Criteria

Inclusion and Exclusion Criteria	Withdrawal Criteria
Inclusion criteria	Preoperative
Age from 18 to 80 BMI from 20 to 39.9 Isolated CABG CPB planned Median sternotomy approach Subsequent admission to ICU	Onset of heart failure Onset of acute decompensated arrhythmia Onset of low oxygen saturation (SpO_2_ < 90%) on supplemental oxygen
Exclusion criteria Severe COPD (PaCO_2_ > 60 mmHg) Recent acute coronary syndrome (<1 week) Acute onset of heart failure Severe anaemia (haemoglobin < 8 g dL^–1^) Preoperative supplemental oxygen required to maintain SpO_2_ >90% Right to left intracardiac shunts Carotid stenosis defined as >50% stenosis of either carotid artery End-stage renal disease requiring haemodialysis Recent smoking (within 1 week) Planned regional anaesthesia	Intraoperative One lung ventilation Additional procedures other than CABG CPB more than once or circulatory arrest Fluid infusion rate more than 10 mL kg^–1^ h^–1^ post CPB Patients in restrictive oxygenation group needing FiO_2_ > 0.7 to maintain SpO_2_ ≥95% SpO_2_ < 90% lasting for more than 5 minutes
	Postoperative Non-respiratory reasons to reintubate Delayed extubation due to bleeding Delayed extubation due to heart failure	Any time Allogenic transfusion except less than 2 units RBC Circulatory assist device implantation (ECMO, VAD, or Impella^®^ device)

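### Randomised patients are taken out of the analysis for events after randomisation, in the name of bias control; this undoes the balance of randomisation and can bias the result either way

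*Protocol article*

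**What the plan says.** The rules are spread over four places in the protocol article.

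- **Intervention and Anaesthetic Regimen.** There is a ceiling on the fluid rate from bypass weaning to the end of surgery; "otherwise, the patient will be withdrawn from analysis". The same section withdraws patients for "Transfusion of more than 2 units of red blood cells (RBCs), fresh-frozen plasma, platelets, or cryoprecipitate within 48 hours of ICU admission".
- **Safety Assessment.** Where SpO2 stays under 90% beyond a 5-minute limit, the rule reads: "at any time during the surgery, the patient will be withdrawn, and this will be recorded as a serious adverse event". Also withdrawn are patients with one-lung ventilation, added procedures, circulatory arrest, repeated bypass, assist devices, delayed extubation, major bleeding or heart failure, and those with "perioperative allogenic RBC transfusion of more than 2 units or if a patient receives any other blood products".
- **Table 2.** The transfusion criterion reads "Allogenic transfusion except less than 2 units RBC". A further intraoperative criterion applies to the restrictive arm alone: needing FiO2 above 0.7 to hold SpO2 at 95% or more.
- **Discussion.** After the rules on return to bypass, circulatory arrest and mechanical support, it says of transfused patients that "these patients will also be withdrawn from our analysis". It then gives the rationale: "We predict a high rate of withdrawal, not only for safety reasons but also for bias control and balancing of confounding factors".

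The Sample Size Calculation treats withdrawals as losses: 200 are recruited to cover 160. No section says that a withdrawn patient is still followed or stays in any analysis.

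**The concern.** Every one of these events except the preoperative criteria in Table 2 arises during or after the assigned strategy. Removing patients because of them does not balance confounders. It replaces two randomised groups with two groups selected on what happened under treatment.

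The selection can differ by arm, for three reasons.

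- The FiO2 above 0.7 rule exists in one arm only. By definition it removes restrictive patients who oxygenate poorly, which would flatter that arm.
- Intraoperative hypoxaemia can plausibly depend on the assigned FiO2. In the other direction, the Introduction says hyperoxia can cause myocardial injury, so removing heart failure could hide harm in the liberal arm.
- The intraoperative triggers arise under anaesthesia staff who know the assignment (Study Design and Setting).

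In addition, withdrawing patients for delayed extubation cuts off the upper tail of a secondary outcome, the length of mechanical ventilation.

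At stake is whether the primary comparison answers the randomised question, or describes only patients with an uneventful course.

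**Working it through.** **Inputs from the plan (Sample Size Calculation):** difference 30 mmHg, SD 60 mmHg, two-sided α 0.05, 80% power, 80 per arm needed, 100 per arm recruited.

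**Inputs assumed, because the article says only that the rate will be high:** the withdrawal rate q, and the correlation ρ (0.3, 0.5, 0.7) between the withdrawal trigger and the lowest PaO2/FiO2.

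**Step 1. The plan's own figure.** The standardised effect is 30/60 = 0.5. A two-sided t-test at 80% power needs 63.8, so 64 per arm (128 in total), not 80 per arm. With 80 per arm the power is 88.2%. The stated 160 does not reproduce, but that is a separate matter. Here it only shows that loss of power is not the problem.

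**Step 2. Selection model.** Within each arm the patients with the worst value of a trigger variable (standard normal) are withdrawn, below a cut-point c. The retained mean rises by ρ × 60 × λ(c), with λ(c) = φ(c)/(1 − Φ(c)).

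**Step 3. True difference 30 mmHg, same cut-point in both arms.** The trigger means lie at ±0.25ρ, so

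observed difference = 30 + 60ρ[λ(c − 0.25ρ) − λ(c + 0.25ρ)].

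The worse arm then loses more patients. Example with q = 20% and ρ = 0.7: rates are 15% and 25%, and 30 + 42 × (0.277 − 0.421) ≈ 24.

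| Overall withdrawal | ρ = 0.3 | ρ = 0.5 | ρ = 0.7 |
|---|---|---|---|
| 20% | 28.9 | 26.9 | 23.9 |
| 30% | 28.6 | 26.2 | 22.6 |

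**Step 4. No true difference, unequal withdrawal.** λ is 0.195 at 10%, 0.350 at 20% and 0.497 at 30%. The spurious difference is 60ρ × (difference in λ). For 20% against 10% at ρ = 0.5: 30 × (0.350 − 0.195) ≈ 4.6 mmHg.

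| Withdrawn, arm 1 v arm 2 | ρ = 0.3 | ρ = 0.5 | ρ = 0.7 |
|---|---|---|---|
| 20% v 10%: shift (mmHg) | 2.8 | 4.6 | 6.5 |
| type I error | 6.1% | 8.3% | 12.1% |
| 30% v 10%: shift (mmHg) | 5.4 | 9.1 | 12.7 |
| type I error | 8.9% | 17.0% | 31.7% |

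The shift favours the arm that loses more patients and changes sign when the arms are swapped. With 10% withdrawn from the restrictive arm, 30% from the liberal arm and ρ = 0.5, a true 30 mmHg is estimated as 20.9. With no true effect and equal rates of equally sick patients, the shift is zero.

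**Step 5. Analysing everyone.** With 100 per arm, power for 30 mmHg is 94.0%, or 92.9% if 5% of primary outcomes are missing in each arm. If complicated patients diluted the difference to 24 mmHg (effect 24/60 = 0.4), power would still be 80.4%.

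**Step 6. Is the analysed set defined?** Not consistently.

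- *Transfusion.* Exactly 2 units of red cells are not a trigger in Intervention and Anaesthetic Regimen or in Safety Assessment (both say more than 2), but are one in Table 2 (only fewer than 2 allowed). The time windows also differ: 48 hours from ICU admission, perioperative, any time. For other products, Safety Assessment withdraws for any amount. In Intervention and Anaesthetic Regimen it is unclear whether the 2-unit limit governs the whole list.
- *Heart failure.* Safety Assessment names its development after surgery; Table 2 names, postoperatively, only delayed extubation due to it.
- *FiO2.* The Abstract gives 0.80 as the upper limit in the restrictive arm, with exceptions; Table 2 withdraws above 0.7.

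**The case against.** The strongest reply has four parts.

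1. **Literal scope.** Removal from the analysis is stated in those words only for fluid rate and transfusion. For hypoxaemia and heart failure the text says withdrawn, and for return to bypass withdrawn from the study. A reader might infer that the article expressly deletes all of these from the analysis; it does not. Exclusion is still the natural reading: the Discussion says that transfused patients are *also* withdrawn from analysis, directly after the bypass and support-device rules, and no section keeps anyone in.
2. **Blinding.** A reader might infer that unblinded staff control every trigger. The article unblinds the operating-room physicians and the centre principal investigators, but blinds the ICU physicians, who would make the ICU transfusion decisions. Red-cell thresholds are also fixed. The point about unblinded staff stands for intraoperative triggers only.
3. **Size.** All rates and correlations are assumed. At ρ = 0.3 the attenuation is about 1 mmHg in 30. A correlation of 0.7 is strong for a mix that includes surgical triggers such as one-lung ventilation. Step 3 shows attenuation only; a spurious effect needs unequal withdrawal. All of this stands, but a trigger written for one arm makes equal withdrawal hard to assume.
4. **Safety and power.** A reader might infer that safety information is lost or the trial underpowered. Intraoperative hypoxaemia is recorded as a serious adverse event, the monitoring board reviews all enrolled subjects, and 80 per arm gives 88% against a planned 80%. Neither inference is supported.

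An unseen analysis plan does not answer the point, because the rule and its rationale are stated here.

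**Conclusion.** The point holds and should be corrected before recruitment. The article prescribes deletion from the analysis for post-randomisation events and justifies it by a purpose that it defeats. The direction of bias cannot be known in advance: the one-arm FiO2 rule and the hypoxaemia rule could favour the restrictive arm, and the heart failure rule could hide harm in the liberal arm.

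Against the plan's own target of 30 mmHg, plausible distortions run from about 1 to 7 mmHg of attenuation under a common withdrawal threshold. Under the unequal rates examined, the spurious difference runs from about 3 to 13 mmHg. These are illustrations conditional on assumed rates of 10–30% and correlations of 0.3–0.7, not predictions. The fault in the rule does not depend on them.

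**What to change.** - Define the primary analysis as all randomised patients who had surgery, in the assigned group, whatever happened later.
- State that scheduled blood gases, pulmonary complications, ventilation, ICU and hospital stay and day-7 status continue to be collected after any withdrawal trigger. The article does not say this now.
- Separate leaving the assigned strategy from leaving the analysis. Any clinical decision to stop the assigned strategy stays as it is; only the analysis set and follow-up change.
- Use the withdrawal criteria only to define a secondary per-protocol set, and report withdrawals by arm and reason.
- Delete the statement that withdrawal controls bias and balances confounders.
- Reconcile the transfusion criteria (Intervention and Anaesthetic Regimen, Safety Assessment, Table 2), the heart failure criteria (Safety Assessment, Table 2) and the FiO2 limits (Abstract, Table 2).

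**Cost:** changes of wording, plus continued collection of assessments already scheduled. Complicated patients may add outcome variance or dilute the difference. With 100 per arm the plan has room for this: 94% power at 30 mmHg, and still 80% if the difference fell to 24 mmHg.

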## Figures and Tables

**Figure 1. f1-tjar-51-2-112:**
[figure not shown]
Algorithm and timetable for enrolment, allocation to restrictive or liberal oxygenation groups, intraoperative management, and postoperative data collection.

**Table 1. t1-tjar-51-2-112:** The Schedule of Enrolment, Interventions, and Outcome Assessment in Different Periods of This Trial

	Enrolment	Allocation	Post-allocation			Close-out
Timepoint	Preoperative 1 Day Before Surgery	Before Oxygenation	Intraoperative	Postoperative 0 hours, 4 hours, 8 hours,12 hours, 24 hours, 48 hours	Discharge	Postoperative 7 Days
Enrolment						
Eligibility screen	**X**					
Informed consent	**X**					
Allocation		**X**				
Interventions						
Restrictive oxygenation group			**X**			
Liberal oxygenation group			**X**			
Assessments						
PaO_2_/FiO_2_ (ABG)		**X**	**X**	**X**		
Postoperative pulmonary complications				**X**	**X**	
Length of mechanical ventilation					**X**	
ICU stay					**X**	
Hospital stay					**X**	
Mortality						**X**

ABG, arterial blood gas; ICU, intensive care unit.

**Table 2. t2-tjar-51-2-112:** Inclusion, Exclusion, and Withdrawal Criteria

Inclusion and Exclusion Criteria	Withdrawal Criteria
Inclusion criteria	Preoperative
Age from 18 to 80 BMI from 20 to 39.9 Isolated CABG CPB planned Median sternotomy approach Subsequent admission to ICU	Onset of heart failure Onset of acute decompensated arrhythmia Onset of low oxygen saturation (SpO_2_ < 90%) on supplemental oxygen
Exclusion criteria Severe COPD (PaCO_2_ > 60 mmHg) Recent acute coronary syndrome (<1 week) Acute onset of heart failure Severe anaemia (haemoglobin < 8 g dL^–1^) Preoperative supplemental oxygen required to maintain SpO_2_ >90% Right to left intracardiac shunts Carotid stenosis defined as >50% stenosis of either carotid artery End-stage renal disease requiring haemodialysis Recent smoking (within 1 week) Planned regional anaesthesia	Intraoperative One lung ventilation Additional procedures other than CABG CPB more than once or circulatory arrest Fluid infusion rate more than 10 mL kg^–1^ h^–1^ post CPB Patients in restrictive oxygenation group needing FiO_2_ > 0.7 to maintain SpO_2_ ≥95% SpO_2_ < 90% lasting for more than 5 minutes
	Postoperative Non-respiratory reasons to reintubate Delayed extubation due to bleeding Delayed extubation due to heart failure	Any time Allogenic transfusion except less than 2 units RBC Circulatory assist device implantation (ECMO, VAD, or Impella^®^ device)

BMI, body mass index; CABG, coronary artery bypass graft; COPD, chronic obstructive pulmonary disease; CPB, cardiopulmonary bypass; ECMO, extracorporeal membrane oxygenation; ICU, intensive care unit; RBC, red blood cell; VAD, ventricular assist device.

**Table 3. t3-tjar-51-2-112:** Definition of Postoperative Pulmonary Complications

Complications	Definitions or Diagnostic Method
Respiratory infection	Antibiotics for suspected infection with 1 or more of the following: new or changed sputum, new or changed lung opacities, fever, white blood cell count >12 × 109 L^–1^
Atelectasis	Lung opacification with mediastinal shift, hilum or hemidiaphragm shift towards the affected area, with compensatory hyperinflation in adjacent non-atelectatic lung
Pneumonia	Chest x-ray with at least 1 of the following: infiltrate, consolidation, and cavitation, plus at least 1 of the following: fever >38˚C with no other cause, white cell counts 12 × 10^9^ L^–1^, and >70 years of age with altered mental status with no other cause plus at least 2 of the following: new purulent/ changed sputum, increased secretions/suctioning, new/worse cough/dyspnoea/tachypnoea, rales/bronchial breath sounds, and worsening gas exchange
Noncardiogenic pulmonary oedema	Evidence of fluid accumulation in the alveoli with enough cardiac output
Pleural effusion	Chest x-ray with blunting of costophrenic angle, loss of sharp silhouette of the ipsilateral hemidiaphragm in upright position, displacement of adjacent anatomical structures, or (in supine position) hazy opacity in 1 hemithorax with preserved vascular shadows
Respiratory failure	Postoperative PaO_2 _< 60 mm Hg on room air
Acute respiratory distress syndrome	PaO_2_/FiO_2_ ratio < 300 mm Hg

Adapted from Jammer (2015).^12^
